To assess uncertainty around the ICER, nonparametric bootstrapping will be applied using a customized Microsoft Excel spreadsheet. ^[119]^ This will involve generating 5000 randomly resampled data sets (1000 samples for each of the five imputed data sets). Each of the 5000 bootstrapped cost-utility pairs will then be graphed on the cost-effectiveness plane ^[118,120,121]^. A cost-effectiveness acceptability curve will then be generated to determine the probability that the STOPS treatment approach for LBP is cost-effective compared with usual.

***Analysis of qualitative data***

The qualitative data will be analyzed using content analysis^[122]^. The interview documents will be read several times by the investigators to understand the texts and the meaning of the content according to the local context. In the next step, the documents will be combined into meaningful and understandable units which will be labelled as codes. The coding process will be performed by two investigators separately, and then compared, and discussed and consensus will be reached within the research team. In the third step, the codes will be synthesized in detail and will be grouped into meaningful sub-categories and labelled with appropriate titles. In the fourth step, subcategories will be merged into broader categories which will finally be pooled into major emerging themes.

***Analysis of fMRI data***

Data will be preprocessed and analyzed using SPM12 (the welcome department of cognitive neurology, London, UK, <http://www.fil.ion.ucl.ac.uk/spm/software/spm12/>). The preprocessing pipeline used will be the standard conventional preprocessing pipeline in using the CONN-fMRI functional connectivity toolbox (http://www.nitrc.org/projects/conn).

All functional images will be slice-time corrected and realigned to the first volume using a six-parameter rigid body transformation. The anatomical image and functional images will be coregistered for the corresponding time-point. Segmented gray matter and white matter images of all participants will be used to construct a tissue probability maps. The template will be normalized to Montreal Neurological Institute (MNI) space and all images, anatomical and functional, will be normalized to this template using the according flow fields. The smoothing kernel for the functional images will be kept as 6 mm and 2 mm for the anatomical image. 2.5.

Functional connectivity analyses will be carried out using the CONN-fMRI functional connectivity toolbox v14. Seed-to-voxel and ROI-to-ROI functional connectivity maps will be created for each participant. The ROI-to-ROI analysis will be used to identify possible differences between before and after treatment. For this analysis we will use all the provided areas. The mean BOLD time series will be computed across all voxels within each ROI.

Individual seed-to-voxel and ROI-to-ROI maps will be entered into a second-level analysis. A within group ROI-to-ROI analysis will be performed. Seed-to-voxel analyses will be as necessary.

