## Methods

## 2.1 Study design

This study is blinded, two armed parallel Randomized Controlled Trial (RCT), will examine the effectiveness of Specific Treatments for the Problems of Spine (STOPS) Physiotherapy care for the management of Low Back Pain (LBP) in comparison with standard physiotherapy (usual care).An overview of process of study is presented in Figure 1.

Assessed for eligibility

(n = …)

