## 2.8 Baseline evaluation

In addition to demographic and general health information of the participant, all the outcome measures (Table 2) provided below will be evaluated at baseline for both STOPS group as well as standard physiotherapy group. All the baseline assessment will be performed by a Physiotherapist who has a minimum of bachelor level degree and blinded allocation of the groups.

| **Patients’ outcome measures** | |
| --- | --- |
| **Outcome measures** | **Measurement points (**weeks) |
| **Primary outcome measures** | |
| 1. Oswestry Disability Index V2.1 with “sex life” question replaced by a “work/housework” question | 0, 5, 10, 26 and 52 |
| 2.Back pain and leg pain intensity :NPRS | 0, 5, 10, 26 and 52 |
|  |  |
| 3. Resting state functional MRI | 0,26 |
| **Secondary outcome measures** | |
| 1. Brief Pain Inventory | 0, 5, 10, 26 |
| 1. Global rating of change scale (7-point Likert scale) | 5, 10, 26 |
| 1. Satisfaction with treatment (5-point Likert scale) | 5, 10, 26 |
| 1. Interference with work or housework in the past week (5-point Likert scale) and number of hours missed at work in past week. | 0, 5, 10, 26 |
| 1. Örebro Musculoskeletal Pain Screening Questionnaire (ÖMPSQ-SF) | 0, 5, 10, 26 |
| 1. Quality of life (EuroQol-5D-5L) | 0, 5, 10, 26 |
| 1. Depression Anxiety and Stress Scale (DASS-21) | 0, 5, 10, 26 |
| 1. Pain Self-Efficacy questionnaire (PSEQ) | 0, 5, 10, 26 |
| 1. Pain Catastrophizing Scale (PCS) | 0, 5, 10, 26 |
| 1. Insomnia Severity Index (ISI) | 0, 5, 10, 26 |
| 1. Central Sensitisation Inventory (CSI) | 0, 5, 10, 26 |
| 1. Clinical inflammation score | 0, 5, 10, 26 |
| 1. Treatment Credibility Questionnaire | 5, 10, 26 |
| 1. Healthcare utilisation | 5, 10, 26 |
| 1. Compliance with treatment | 5, 10, 26, 52 |
| 1. Resting state functional MRI | 0, 26 |
| 1. Qualitative interviews | At the end of treatment trial 10 |
| 1. Adverse event | 5, 10, 26 |

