***Primary outcomes***

Activity limitation will be evaluated using nine questions from the Oswestry Disability Index Version 2.1^[66,67]^, with the tenth question relating to “sex life” being replaced by a question relating to “work/housework”.^[67,68]^ The Oswestry is a reliable, valid, and responsive instrument for measuring activity limitation in people with low back pain and referred leg pain.^[69-71]^

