16. *Compliance with treatment:* The number of treatment sessions attended, and the number of missed or cancelled appointments by each patient will be recorded by the physiotherapists. Patient compliance with the treatment will be reviewed by the physiotherapists at each follow-up visit via direct questioning (on a scale of 0-10, how adherent have you been with following the advice and exercises recommended by your physiotherapist on average over the last month? from “not at all” to “fully”) and by reviewing the patient’s exercise charts ^[14,56]^.
17. Resting state functional MRI data (only for a cohort).Details under (Appendix 4)
18. *Qualitative interviews:* A qualitative study of therapist and patients’ experiences will be nested within the usual care program and quality improvement programme using a semi-structured questionnaire and interviews. Individual interviews lasting for 30-40 minutes will be conducted by a different researcher who has experience in qualitative interviews but was not involved in treating patients in the study. Interviews will be voice recorded, and transcribed verbatim, before undergoing thematic analysis. All discussions will be directed by a flexible topic guide (Appendix 3) developed from the pertinent literature ^[110-113]^. The topic guide comprises semi-structured non-leading questions phrased in clear language.
19. *Adverse events:* Continuous clinical assessment of adverse effects events (harmful or unpleasant) of treatment will be monitored by treating physiotherapists and recorded in their participant clinical notes, per their standard clinical practice. Physiotherapists will routinely enquire with participants each session about their response to treatment and any adverse effects of treatment or prescribed exercises.

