**Data acquisition**

Functional and structural (T1 EMPIRAGE) images will be acquired for each participant. The protocol for the data acquisition (Philips ingenia 3T specific) will be adopted from Alzheimer’s Disease Neuroimaging Initiative (ADNI) 3 protocol (1). The scanning duration will be kept as more than 10 minutes to ensure the reliability.

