**Connectivity Analysis**

Functional connectivity analyses will be carried out using the CONN-fMRI functional connectivity toolbox v14. Seed-to-voxel and ROI-to-ROI functional connectivity maps will be created for each participant. The ROI-to-ROI analysis will be used to identify possible differences between before and after treatment. For this analysis we will use all the provided areas. The mean BOLD time series will be computed across all voxels within each ROI.

Individual seed-to-voxel and ROI-to-ROI maps will be entered into a second-level analysis. A within group ROI-to-ROI analysis will be performed. Seed-to-voxel analyses will be as necessary.

1. ADNI. MRI scanner protocols 2022 [Available from: <https://adni.loni.usc.edu/methods/documents/mri-protocols/>.

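### The only contrast named for resting state fMRI is before versus after within group, which does not estimate the STOPS versus usual-care difference

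*Protocol*

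**What the plan says.** Section 2.1 sets the question as STOPS "in comparison with standard physiotherapy (usual care" being the comparator, in a two-arm parallel randomised trial.

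The protocol gives fMRI more than one status. Table 2 (section 2.8) has "3. Resting state functional MRI" in its primary block, at weeks 0 and 26, and lists the same measure again in its secondary block. Under Primary outcomes, section 2.12 names only the Oswestry: "Activity limitation will be evaluated using nine questions from the Oswestry Disability Index Version 2.1". It puts fMRI at secondary item 17: "Resting state functional MRI data (only for a cohort", with a pointer to Appendix 4.

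The fMRI analysis has its own heading in section 2.15, and Appendix 4 repeats the text. The aim is stated as follows: "The ROI-to-ROI analysis will be used to identify possible differences between before and after treatment". On the regions: "For this analysis we will use all the provided areas". After saying that individual maps go into a second-level analysis, the text ends: "A within group ROI-to-ROI analysis will be performed. Seed-to-voxel analyses will be as necessary".

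**The concern.** For the other quantitative outcomes the protocol names a comparison of the arms: a group by time mixed model for continuous clinical outcomes, and between-group differences for costs and QALYs. For fMRI it names only change within a group. An analyst who followed that section would have two before-and-after results and no estimate of how the arms differ.

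A change from week 0 to week 26 within an arm has several possible sources besides treatment: the natural course of the condition, regression to the mean in people enrolled while symptomatic, and drift in the scanner over six months. Randomisation balances these between arms in expectation, but only a contrast between arms makes use of that balance. At stake is whether two scans per scanned participant can say anything about STOPS relative to usual care.

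**Working it through.** The protocol states no figure on this point, so there is none to reproduce. The check has three steps.

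**1. The sections side by side**

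| Place | Contrast named |
|---|---|
| 2.1 Study design | STOPS versus usual care |
| 2.15, clinical outcomes | Group by time; between-group effects at 5, 10 and 26 weeks |
| 2.15, cost-effectiveness | Between-group differences in costs and QALYs |
| 2.15, fMRI | Before versus after; within group |
| Appendix 4, Connectivity Analysis | Before versus after; within group |

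The group by time model stands under the heading for patients' clinical outcomes. fMRI has a separate heading, separate software and its own stated contrast, so that model does not carry over to it.

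**2. What each contrast estimates**

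Let c be the mean change that would occur in either arm without a treatment effect (natural course, regression to the mean, drift). Let e_S and e_U be the effects of STOPS and usual care.

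- Within STOPS: c + e_S
- Within usual care: c + e_U
- Difference in change: (c + e_S) − (c + e_U) = e_S − e_U

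Only the third line is free of c, and it is the randomised comparison.

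**3. Size of the problem if the two within-arm results are set side by side**

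Suppose both arms truly change by the same amount and each within-arm test has power p. With independent arms, the chance that exactly one is significant is 2p(1 − p):

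- p = 0.50: 2 × 0.50 × 0.50 = 0.50
- p = 0.80: 2 × 0.80 × 0.20 = 0.32
- p = 0.99: 2 × 0.99 × 0.01 = 0.02

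By symmetry, STOPS is the significant arm in half of these cases.

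A simulation of 20,000 trials per row agrees. It takes one connectivity measure, normal change scores with SD 1, the same true mean change in both arms, and tests at 0.05. Arm sizes and mean changes are assumptions, because the protocol gives neither a cohort size nor an fMRI effect size.

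| n per arm | Mean change (SD) | Within-STOPS test significant | Exactly one arm significant | Between-arm test significant |
|---|---|---|---|---|
| 15 | 0.3 | 19% | 31% | 5% |
| 15 | 0.5 | 44% | 49% | 5% |
| 30 | 0.3 | 36% | 46% | 5% |
| 30 | 0.5 | 75% | 37% | 5% |
| 75 | 0.3 | 73% | 40% | 5% |
| 75 | 0.5 | 99% | 2% | 5% |

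With no difference between the arms, the within-STOPS test is significant in 19% to 99% of trials. Exactly one arm is significant in 2% to 49%. The test of the difference in change holds its level throughout.

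**The case against.** The best defence is that fMRI is a secondary sub-study. Section 2.12 names only the Oswestry as primary, section 2.13 describes the primary outcomes as disability, and fMRI is confined to a cohort. This stands in part. A reader who sees only the primary block of Table 2 might infer that a settled primary outcome lacks a valid analysis, but the same table and section 2.12 also list it as secondary. The lower status reduces the stakes, yet a secondary outcome of a randomised comparison still needs a contrast between arms.

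It can also be said that maps entered into a second-level analysis could include a between-group contrast. Nothing forbids one, so it would go too far to say that the protocol rules it out. But none is named, and the next sentence says which analysis will be run. Nor is this detail left to a statistical analysis plan, because the protocol itself fixes the contrast, in two places.

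Three stronger readings are not supported:

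- A reader might infer from the use of all provided areas that many false positives will follow. The protocol states neither a number of regions nor a significance threshold, and multiplicity control may properly be left to the SAP.
- A reader might infer that Appendix 4 contradicts section 2.12, since "images will be acquired for each participant". Section 2.12 refers to that appendix for the cohort's details, so the phrase can naturally mean each scanned participant. One clarifying phrase is enough.
- A reader might infer that the arms will commonly disagree on significance. That depends on the within-arm power: the figure is as low as 2% when power is near 99%, and it applies to a single measure, not to a whole connectivity map. The protocol does not say that the two within-arm results will be compared in this way.

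**Conclusion.** The point holds. As written, sections 2.15 and Appendix 4 give fMRI a before-and-after analysis within group, which does not estimate the comparison that the trial was randomised to make. That conclusion rests on the text alone and needs no assumed number.

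The size of the misreading does rest on assumptions: equal true change in both arms, independent arms, and a within-arm power that the documents do not allow one to fix. On those terms exactly one arm is significant in about 2% to 50% of cases, against 5% for a direct test of the difference. How much this matters depends on the unresolved status of fMRI: more if it is primary, less if it is secondary in a cohort. In either case the change should be made.

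**What to change.** In section 2.15 (Analysis of fMRI data) and in Appendix 4 (Connectivity Analysis):

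- Make the main second-level analysis a group by time contrast: week 26 minus baseline, STOPS minus usual care.
- Keep the within-group maps as descriptive results.
- Label seed-to-voxel analyses exploratory.

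In Table 2 and section 2.12, list fMRI once, as either primary or secondary. State in Appendix 4 that the acquisition and analysis apply to the scanned cohort.

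The same scans and toolbox serve, so the direct cost is wording and a different contrast. The statistical cost is lower apparent sensitivity: with n per arm and equal variances, the standard error of the difference in change is √2 ≈ 1.41 times that of the change in one arm. No cohort size is given, so the estimate may be imprecise if few participants are scanned. It would still address the trial's question, which the before-and-after result does not.

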## APPENDIX 1: PHYSICAL EXAMINATION & OUTCOMES

| **PHYSICAL EXAMINATION** |
| --- |
| The physical examination will involve:   1. Observation of the spine for evidence of postural deformity such as a lateral shift or an increased or decreased lumbar lordosis [1], using protocols with acceptable reliability [2,3]. 2. Measurement of lumbar spine active movements into flexion, extension and lateral-flexion using finger-to-floor measurement methods that have been shown to be reliable [4]. 3. Lower limb neurological examination in a seated position, which will involve testing of knee jerk and ankle jerk reflexes, myotomal strength testing and dermatomal sensation in response to light touch with a tissue [5]. Acceptable reliability for these tests has been demonstrated in people with suspected lower limb nerve root compression [5]. 4. Straight leg raise and crossed straight leg raise, which will be considered positive if the participant’s usual lower limb symptoms are reproduced at any angle during passive raising of either leg by the examiner [5]. The reliability of this test is considered good when performed on people with suspected nerve root compression [5]. 5. Prone knee flexion test, which will be considered positive if the participant’s usual anterior thigh symptoms are reproduced at any angle [6,7]. The reliability of this test has been shown to be good in people with suspected nerve root compression [5]. 6. Lumbar spine palpation performed with the participant prone, with the examiner applying pressure centrally over the lumbar spinous processes and unilaterally over the lumbar zygapophyseal joints and/or transverse processes [8]. Where a localised painful or stiff segment is identified, a “mini-treatment” will be undertaken consisting of a 30-second low grade mobilization of the joint, and the participant’s response will be recorded in terms of any changes in pain or range of motion upon repeat testing [9,8]. Studies have demonstrated good reliability for lumbar spine palpation [10,11]. 7. Mechanical loading strategies including sustained prone positioning and repeated extension movements in a prone position (with or without lateral shift of the pelvis), which will be assessed to determine whether a directional preference is present. Directional preference will be defined as the direction of movements or postures that result in either centralisation of symptoms, sustained decrease in symptoms (by at least 1 point on a 0-10 numerical rating scale) or improvement in range-of-motion following the assessment of mechanical loading strategies [12-14]. Assessing for a directional preference has been shown to be reliable [14,15]. 8. Determination of the participant’s ability to activate the transversus abdominis via a localised inward movement of the lower abdominal wall in a standing position which will be visualised and palpated using a reliable method [16,17]. Each participant’s ability to activate the lumbar multifidus via localised generation of tension will also be assessed via palpation of the participant in prone. Although therapist palpation is one recommended method of assessing the activation of multifidus [17], studies evaluating the reliability of this method could not be located. |


## APPENDIX: PATIENT REPORTED OUTCOMES

| **INITIAL PATIENT QUESTIONNAIRE** | | | | | | | | | | | |
| --- | --- | --- | --- | --- | --- | --- | --- | --- | --- | --- | --- |
| **Your details Patient Trial ID number _______________** | | | | | | | | | | | |
| **Title** | Mr | Mrs | | Family name (surname) | | | | | **Given name(s)** | | |
|  | Ms | Miss | |  |  |  |  |  |  |  |  |
| **Gender** | |  | | Date of birth *(dd/mm/yyyy)*__ __ /__ __ / __ __ __ __ | | | | | Today’s date *(dd/mm/yyyy)*__ __ /__ __ / __ __ __ __ | | |
|  | Male | Female | |  |  |  |  |  |  |  |  |
| Level of education | Primary | Secondary | | Tertiary (university) | | | | | None | | |
| What is your occupation? …………………………………………………………………………………………………… | | | | | | | | | | | |
| Annual household income?………………………………………………………………………………………………. | | | | | | | | | | | |
| Home address ………………………….………………………………………………………………………………………………………………………………. ………………………………………………………………………………………………………………………………………………………………….……………….  **Phone:** Home: ……………………………… Work: ……………………………….……….… Mobile: …………………………………..………………  **Email** ……………………………………………………………………………………………………………………………………………………………………….. | | | | | | | | | | | |
| **Country of Birth…………………………………………………………………………………………………………………….** | | | | | | | | | | | |
| **Do you require an interpreter?** | | | | | Yes | No | | | | | |
| *If you answered yes, please specify the language*………………………………………………………………… | | | | | | | | | | | |
| **Are you hearing or sight impaired?** | | | | | Yes | No | | | | | |
| **Do you require help with written or spoken communication?** | | | | | | | Yes | | | No | |
| **Tobacco use status (including smoking):**  Current user | | | | | | | Previous user | | | No | |
| **Height** *(in cm)* | | | **Weight** *(in kg)* | | | | | | | | |
| **Is there a compensation case relating to this episode?** | | | | | | | Yes | | | No | |
| **Marital status** | | | | Married | | | Unmarried | | | | |
|  |  |  |  | Divorced | | | Widow / widower | | | | |
| **How did your main pain begin?** | | | | | | | | | | | |
| Injury at home | | | | Car crash | | |  | | | | |
| Injury at work/school | | | | No obvious cause | | | |  | | | |
| Injury in another setting | | | |  | | |  | | | | |
| **How long has your main pain been present?** *(Tick* ***one*** *box only)* | | | | | | | | | | | |
| Less than 3 months | | | | 12 months to 2 years | | | More than 5 years | | | | |
| 3 to 12 months | | | | 2 to 5 years | | |  | | | | |
| Which statement best describes your pain? *(Tick* ***one*** *box only)* | | | | | | | | | | | |
| Always present (always the same intensity) | | | | | | | | | | | |
| Always present (level of pain varies) | | | | | | | | | | | |
| Often present (pain free periods last less than 6 hours) | | | | | | | | | | | |
| Occasionally present (pain occurs once to several times per day, lasting up to an hour) | | | | | | | | | | | |
| Rarely present (pain occurs every few days or weeks) | | | | | | | | | | | |
| **Do you have any of the following?** | | | | | | | | | | | |
| A mental health condition, in particular:  PTSD Anxiety   Depression  Other *(please specify)*………………………………………………………………………………………………… | | | | | | | | | | | |
| Arthritis *(including Rheumatoid/Osteoarthritis)* | | | | | | | | | | | |
| Muscle, bone and joint problems other than arthritis *(including Osteoporosis, Fibromyalgia)* | | | | | | | | | | | |
| Heart and circulation problems *(including Heart Disease, Pacemaker, Blood Disease)*  In particular specify if you have:  High Blood Pressure  High Cholesterol | | | | | | | | | | | |
| Diabetes | | | | | | | | | | | |
| Digestive problems *(including IBS, GORD, Stomach Ulcers, Reflux, Bowel Disease)* | | | | | | | | | | | |
| Respiratory problems *(including Asthma, Lung Disease, COPD, Sleep Apnoea)* | | | | | | | | | | | |
| Neurological problems *(including Stroke, Epilepsy, Multiple Sclerosis, Parkinson’s Disease)* | | | | | | | | | | | |
| Cancer | | | | | | | | | | | |
| Liver, kidney and pancreas problems *(including Pancreatitis, Kidney Disease)* | | | | | | | | | | | |
| Thyroid problems *(including Hyperactive or Hypoactive Thyroid, Graves’ Disease)* | | | | | | | | | | | |
| Any other medical conditions *(please specify)*………………………………………………………………… | | | | | | | | | | | |
| **Health care *(other than your visits to this clinic)*** | | | | | | | | | | | |
| 1. How many times in the past 3 months have you seen a general practitioner about your pain? | | | | | | | | | | | ……… times |
| 1. How many times in the past 3 months have you seen a medical specialist (e.g. orthopaedic surgeon) in regard to your pain? | | | | | | | | | | | ……… times |
| 1. How many times in the past 3 months have you seen health professionals other than doctors (e.g. physiotherapist, chiropractor, psychologist) in regard to your pain? | | | | | | | | | | | ……… times |
| 1. How many times in the past 3 months have you visited a hospital emergency department in regard to your pain? *(Include all visits, regardless of whether or not you were admitted to the hospital from the emergency department)* | | | | | | | | | | | ……… times |
| 1. How many times in the past 3 months have you been admitted to hospital because of your pain? | | | | | | | | | | | ……… times |
| 1. How many diagnostic tests (e.g. X-rays, scans) have you had in the last   3 months relating to your pain? …………. tests   1. Have you ever had surgery on your back?  Yes  No 2. Have you ever had injections into your back?  Yes  No | | | | | | | | | | |  |

| Prior to commencing in this trial, how satisfied have you been with your overall healthcare / treatment for your current episode of low back pain or leg symptoms (sciatica)? (tick one box)   Very  Somewhat  Neither satisfied  Somewhat  Very  dissatisfied dissatisfied nor dissatisfied satisfied satisfied |
| --- |

Please rate your **back** pain by circling the number below that best describes your pain on average over the last week

0 1 2 3 4 5 6 7 8 9 10

*No pain Worst pain possible*

4. Please rate your **leg** pain by circling the number below that best describes your pain on average over the last week

0 1 2 3 4 5 6 7 8 9 10

*No pain Worst pain possible*

| Your work | | | |
| --- | --- | --- | --- |
| **Are you currently employed (have a job to go back to with an employer)?** | | | |
| Yes - If *yes*, are your normal hours:  Working full-time  Working part-time  Please answer the questions below | | No - If *no*, are you:  (tick ***one*** only, then go straight to **Section 3**)  Unable to work due to a condition other than pain  Unable to work due to pain  Not working by choice (student, retired, homemaker)  Seeking employment (I consider myself able to work but cannot find a job) | |
| **During the past seven days, how many hours did you miss from your normal work hours because of problems associated with your pain?**  (Include hours you missed on sick days, times you went in late, left early, etc. because of your pain. *Do not include time you missed to attend this pain clinic).* | | | …………… hours |
| **During the past seven days, how many hours did you actually work?** *(If ‘0’ skip the next question and go to* ***Section 3****)* | | | …………… hours |
| **During the past seven days, how much did your pain affect your productivity while you were working?**  Think about days you were limited in the amount or kind of work you could do, days you accomplished less than you would like, or days you could not do your work as carefully as usual.  If pain affected your work only a little, choose a low number.  Choose a high number if pain affected your work a great deal.  Consider only how much pain affected  productivity while you were working | | | |
| Pain had no effect on my work | 0 1 2 3 4 5 6 7 8 9 10  CIRCLE A NUMBER | | Pain completely prevented me  from working |

| Medication use | | | |
| --- | --- | --- | --- |
| Are you taking any medications?  No *(please go to* ***Section 4****)*  Yes *(Please list all the medications you are taking. Include both prescription and over-the-counter medicines)* | | | |
| Medicine name  *(as on the label)* | Medicine strength *(as on the label)* | How many do you take per day? | How many days per week do you take this medication? |
|  |  |  |  |
|  |  |  |  |
|  |  |  |  |
|  |  |  |  |
|  |  |  |  |
|  |  |  |  |
|  |  |  |  |
|  |  |  |  |
|  |  |  |  |
|  |  |  |  |
|  |  |  |  |
|  |  |  |  |
|  |  |  |  |
|  |  |  |  |
|  |  |  |  |
|  |  |  |  |

| Brief Pain Inventory - Pain intensity and interference | | | | | | | | | | | | | | | | | | | | | | | | | | | | | | | | |  |
| --- | --- | --- | --- | --- | --- | --- | --- | --- | --- | --- | --- | --- | --- | --- | --- | --- | --- | --- | --- | --- | --- | --- | --- | --- | --- | --- | --- | --- | --- | --- | --- | --- | --- |
| **On the diagram below, shade in ALL the areas where you feel pain.** [figure not shown][figure not shown] FRONT VIEW  BACK VIEW  LEFT  RIGHT  RIGHT | | | | | | | | | | | | | | | | | | | | | | | | | | | | | | | | |  |
| **On the diagram below, put an X on the ONE area that hurts most.** [figure not shown][figure not shown] FRONT VIEW  BACK VIEW  LEFT  RIGHT  RIGHT | | | | | | | | | | | | | | | | | | | | | | | | | | | | | | | | |  |
| **Please rate your pain by circling the one number that best describes the following:** | | | | | | | | | | | | | | | | | | | | | | | | | | | | | | | | | |
| 1. Your overall pain at its *worst* in the last week? | 0 | 1 | | 2 | | | | 3 | | 4 | | | 5 | | | | 6 | | | | 7 | | 8 | | | | 9 | | | | 10 | | |
|  | No pain | |  | |  | | | | | | |  | | |  | | | |  | | | | | | Pain as bad as you can imagine | | | | | | | | |
| 1. Your overall pain at its *least* in the last week? | 0 | 1 | | 2 | | | | | 3 | | 4 | | | 5 | | | | 6 | | | | 7 | | 8 | | | | 9 | | | | 10 | |
|  | No pain | |  | |  | | | | | | |  | | |  | | | |  | | | | | | Pain as bad as you can imagine | | | | | | | | |
| 1. Your pain on *average* in the last week? | 0 | 1 | | 2 | | | | 3 | | 4 | | | 5 | | | | 6 | | | | 7 | | 8 | | | | 9 | | | 10 | | | |
|  | No pain | |  | | |  | | | | | |  | | | |  | | | |  | | | | | Pain as bad as you can imagine | | | | | | | | |
| 1. How much overall pain do you have *right now*? | 0 | 1 | | 2 | | | | 3 | | 4 | | | 5 | | | | 6 | | | | 7 | | 8 | | | 9 | | | 10 | | | | |
|  | No pain | |  | | | |  | | | | |  | | | |  | | | |  | | | | | Pain as bad as you can imagine | | | | | | | | |

| **During the past week, how much has pain interfered with the following:** | | | | | | | | | | | | | | | | |
| --- | --- | --- | --- | --- | --- | --- | --- | --- | --- | --- | --- | --- | --- | --- | --- | --- |
| 1. Your general activity? | 0 | 1 | | 2 | 3 | 4 | | 5 | | 6 | | 7 | 8 | | 9 | 10 |
|  | Does not interfere | |  | | | |  | |  | |  | | | Completely interferes | | |
| 1. Your mood? | 0 | 1 | | 2 | 3 | 4 | | 5 | | 6 | | 7 | 8 | | 9 | 10 |
|  | Does not  interfere | |  | | | |  | |  | |  | | | Completely interferes | | |
| 1. Your walking ability? | 0 | 1 | | 2 | 3 | 4 | | 5 | | 6 | | 7 | 8 | | 9 | 10 |
|  | Does not  interfere | |  | | | |  | |  | |  | | | Completely interferes | | |
| 1. Your normal work (both outside the home and housework)? | 0 | 1 | | 2 | 3 | 4 | | 5 | | 6 | | 7 | 8 | | 9 | 10 |
|  | Does not  interfere | |  | | | |  | |  | |  | | | Completely interferes | | |
| 1. Your relations with other people? | 0 | 1 | | 2 | 3 | 4 | | 5 | | 6 | | 7 | 8 | | 9 | 10 |
|  | Does not  interfere | |  | | | |  | |  | |  | | | Completely interferes | | |
| 1. Your sleep? | 0 | 1 | | 2 | 3 | 4 | | 5 | | 6 | | 7 | 8 | | 9 | 10 |
|  | Does not  interfere | |  | | | |  | |  | |  | | | Completely interferes | | |
| 1. Your enjoyment of life? | 0 | 1 | | 2 | 3 | 4 | | 5 | | 6 | | 7 | 8 | | 9 | 10 |
|  | Does not  interfere | |  | | | |  | |  | |  | | | Completely interferes | | |

